## Study phases

As illustrated in Fig. 3 and described below, each site will move through five consecutive phases: (1) implementation as usual, (2) pre-implementation, (3) active implementation, (4) consolidation, and (5) evaluation.

**Fig. 3 Fig3:**
[figure not shown]
Summary of Safer Aging Through Geriatrics-Informed Evidence-Based Practices project phases

### Phase 1: Implementation as Usual (2–20 months depending on site)

Each cluster of sites will begin with an “Implementation as Usual” phase, which will involve rolling out EBPs in the manner that is typical for new program implementation in the VA. Implementation as Usual includes a public relations campaign to raise awareness of the SAGE program and EBPs and connects leadership and front-line staff to EBP-related resources. Dissemination approaches will include using social media (Twitter, VA Pulse), hosting a VISN SharePoint page, sending targeted emails using GovDelivery, and using digital bulletin boards and infographics placed in clinical areas. These communications are commonly used approaches by the VA and similar organizations such as the Agency for Health Research and Quality and the Centers for Disease Control and Prevention [45, 46]. This phase will allow us to capture baseline data (e.g., number of staff accessing the EBP materials), including answering qualitative questions (e.g., “Have you hear about SAGE QUERI? If so, how?”), and allow for measurement of any incremental benefit of the more active (intense) implementation approach in phase 3.

### Phase 2: Pre-Implementation (6–7 months)

Each cluster of sites will undergo a “Pre-Implementation” phase to accomplish three goals: (1) identify barriers and facilitators to implementation, (2) solidify front-line staff support for implementing the EBPs, and (3) build relationships between the implementation team and front-line staff that promote Adoption and Maintenance of the EBPs. Our pre-implementation contextual inquiry will include conducting rapid content analysis of key informant interviews and site visits (e.g., observations, group process mapping, and group pre-mortem brainstorming). Data we collect during the pre-implementation phase will be used to tailor the implementation process at each site during the implementation phase and as baseline data for evaluation.

#### Key informant interviews

To better understand the local context and map processes, we are conducting semi-structured key informant stakeholder interviews with staff virtually at each site. We will use a purposive convenience snowball sampling approach to interview approximately 5 to 10 administrators and clinicians individually per site for each EBP. We are using semi-structured interview guides and parallel memo templates for each EBP based on the PRISM domains (Table 3). For example, questions explore staff’s knowledge and impressions of the EBP, understanding of current practices related to key processes important to each EBP (such as deprescribing for EMPOWER or enrolling patients in caregiver support programs for TAP), perceptions of how the EBP could be integrated into current practice, and general views regarding potential facilitators and barriers to implementation. These interviews are anticipated to last approximately 30 to 60 min, will be audio-recorded, and transcribed for analysis.

#### Site visits

Following the completion of key stakeholder interviews, we are conducting site visits (either in person or virtually) which include informational sessions with leadership, observations of current processes, and group activities with frontline staff. To help garner support, the leadership informational sessions will provide an overview of the EBPs, present historical site-specific quality and performance data related to the EBPs, and provide an opportunity to answer questions. At each site per EBP, trained SAGE staff will conduct observations of key settings and/or staff members to gain an understanding of the context, processes, and interpersonal dynamics of the clinical sites. Informed by rapid ethnographic approaches [23, 47, 48] and the PRISM framework (Table 1), we will use structured tools and unstructured fieldnotes to record observational data.

Additionally, for each EBP, we will use two group activities involving novel rapid site assessment tools informed by PRISM domains—a brainwriting premortem exercise [49] and a process mapping exercise [50, 51]—to further understand the perspectives of frontline staff. The “brainwriting premortem” is a focus group technique that uses silent sharing of written ideas about how a proposed implementation process will fail; it allows stakeholders to express concerns and think through potential barriers in advance. Participants are then invited to brainstorm solutions to the perceived barriers and anticipated failure points [49, 50]. The structured process mapping exercise focuses on how processes currently occur and includes identifying which personnel are involved, how long each step takes in a specific process, and potential failure points. The process maps are also serving as a baseline and can be compared to post-implementation process maps to understand how (and begin to understand why) the process may or may not have changed as a result of implementation activities (i.e., adaptations) [49, 50].

#### Data integration

We are utilizing findings from the key informant interviews, site visit observations, group process mapping, and group pre-mortem brainwriting to create site-specific summaries which will be used to adjust the adaptable components of each EBP. Following key informant interviews and the site visits, two trained SAGE staff members will complete a semi-structured debrief and templated memo to summarize the interview content [52]. Site profiles will then be generated from these summaries to inform the pre-implementation site visits and guide the next steps in implementation [52]. Additionally, a PRISM informed codebook will be developed to guide thematic analysis of interviews. Both the initial rapid content analysis and the more in-depth thematic analysis [53] will be used to gain a better understanding of the different organizational perspectives of the EBPs and organizational contexts to aid in creating a sustainable implementation plan tailored to the unique aspects of each site (Fig. 3).

### Phase 3: Active Implementation (6 months)

Following the pre-implementation assessment, the “Active Implementation” phase beings. To maximize fit between our chosen EBPs and each site, our active implementation strategies focus on facilitation, a flexible implementation strategy with a long track record of success for different EBPs in VA settings [26, 54–56]. It involves a partnership between external facilitators (i.e., SAGE staff) and the site implementation team, including front-line staff and operational leaders, who jointly plan and problem-solve issues related to implementation. We use the information gathered during pre-implementation assessments to inform which facilitation tools and approaches to use at each site. The current study will test the implementation strategies of facilitation, training and technical support, intervention tailoring, and audit and feedback.

#### Facilitation

Facilitation is the process of developing an interpersonal relationship focused on engaged problem-solving and support with the goal to implement an EBP within a given context [57]. Facilitation supports all aspects of implementation, but primarily Reach, Adoption, and Maintenance. For facilitation to achieve sustainable change, it is necessary to utilize a “highly partnered” strategy [58]. Facilitation is considered a multifaceted implementation strategy in that other implementation strategies are often used alongside and integrated with facilitation to support the implementation of an EBP. The SAGE project managers function as the external facilitators and support the implementation team for each EBP at a given site. The implementation team consists of a champion at each site to engage with key stakeholders, front-line staff, and older Veterans. For example, academic detailing pharmacists may act as champions for the EMPOWER intervention, whereas a surgeon and/or palliative care clinician may champion the Surgical Pause program, and a home-based primary care nurse practitioner may champion TAP or CAPABLE. Intervention facilitators will complete facilitation training offered by the VA Behavioral Health QUERI through the Implementation Facilitation hub before commencing facilitation activities.

#### Training and technical assistance

External SAGE facilitators will provide further support by utilizing the additional implementation strategies of training and technical assistance to the implementation teams. For example, training may take the form of education on the Best Case/Worst Case approach to goals of care conversations for the Surgical Pause [59], while TAP and CAPABLE have existing online training modules that are paired with in-person evaluation and demonstration of key skills (https://duo.online.drexel.edu/new-ways-for-better-days/; https://nursing.jhu.edu/faculty_research/research/projects/capable/). The Canadian Deprescribing Network has developed a series of professional videos plus toolkits for the implementation of EMPOWER (Deprescribing.org). Ongoing technical assistance is provided during weekly virtual “office hours” to answer questions related to any EBP or during implementation team calls. Technical assistance supports previous training efforts about each of the EBPs and focuses on ensuring that all relevant providers who adopt the EBP are able to deliver it with high fidelity.

#### Intervention tailoring

Intervention tailoring involves prespecifying changes able to be made to the EBP to support implementation in the local context. This allows for each of the four EBPs to have some degree of adaptability to the local context while still maintaining fidelity. As shown in Table 3, a priori, we defined which aspects of the EBPs are “core” (cannot be modified) and which are “adaptable” (can be tailored to fit local context) to support all RE-AIM outcomes [60]. Based on the findings from the pre-implementation phase, we will work with the EBP developers to help re-define the adaptable elements to tailor the interventions to each site.

#### Audit and feedback

Audit and feedback will provide data on performance and help sites with Reach, Adoption, and measuring preliminary evidence of Effectiveness (i.e., through run or control charts; [57, 61]). We will employ our experience in quality improvement to conduct rapid implementation and evaluation cycles to iteratively improve implementation strategies, particularly early in the Active Implementation phase. For example, we can review the VA medical record to evaluate what proportion of older surgical patients underwent frailty screening; or identify VA pharmacy fills for older Veterans who received the EMPOWER intervention. This approach will help the implementation team at each site to have a timely understanding of how implementation is going and together with the external facilitator problem solve to overcome identified barriers.

#### Data collection

During the active implementation phase, we will track audit-feedback data and collect a range of qualitative data (e.g., recordings of meetings, tracking implementation, qualitative interviews) to better describe and understand the “how” of implementation. Using a standardized tracking form, the evaluation team and external facilitators will track implementation activities such as implementation team meetings (i.e., facilitation), implementation office hours, and facilitation coaching office hours. The SAGE evaluation team will also conduct monthly semi-structured interviews with the EBP external facilitators to understand how the implementation process is progressing and describe lessons learned from each EBP and site. Likewise, the SAGE evaluation team will conduct interviews with the implementing clinicians and Veterans who have received the EBP—which will be used to understand the process of implementation. Last, the SAGE evaluation team will conduct follow-up site visit observations to develop current process maps and serve as a check on implementation fidelity.

### Phase 4: Consolidation (6 months)

In this consolidation phase, sites will have settled on a tailored implementation plan for delivery of the EBPs, and efforts will shift to promoting Maintenance of the EBP implementation (Fig. 3). While sites will receive technical assistance and audit-and-feedback reports during this phase, the goal is to facilitate the transfer of both technical and strategic skills to individuals at each site (e.g., ability to rapidly assess needs/resources, team management, and organizational change). SAGE-initiated support will decline and will transition to rely on implementation team-initiated and on an as-needed basis. The development of a sustainment plan and learning collaboratives will help support this transition.

#### Sustainment plan

The goal of the sustainment plan is to provide the implementation team with the resources and information needed to continue implementation indefinitely. During the first month of the consolidation phase, the external facilitator and implementation team will review the implementation step-by-step process using a worksheet to identify any changes needed to reflect the current implementation process. For example, the sustainment plan will include the following: an updated process map, monthly audit and feedback reports during active implementation, SAGE QUERI SharePoint link, information for ongoing EBP and Implementation Science office hours, and learning collaborative dates.

#### Learning collaboratives

Learning collaboratives across sites will involve monthly calls with the implementation teams working on a specific EBP who have completed the active implementation phase. The goals of the learning collaboratives include the following: (1) to create a space for implementation teams of a given EBP to have a space to engage with and learn from other sites and (2) to build a sustainable knowledge base for the given EBP across the VISN. Agendas for the learning collaborative will initially be driven by the implementation teams and will focus on peer support and problem solving to promote sustained EBP implementation. Learning collaboratives will support Adoption and Maintenance, as well as help us to track implementation adaptations [62].

#### Data collection

The SAGE study team will continue to use the implementation tracking process to document interactions with sites and/or implementation teams during the consolidation phase. While creating the sustainment guides, the external facilitator will ask the implementation team the following: “What would it take for this EBP to be sustained forever?”; “What resources—such as supports or information—are needed?”; “What additional resources can the SAGE team provide you?” This information will be recorded in a debrief form.

### Phase 5: Evaluation (12 months)

The study will conclude with the “Evaluation” phase. We will evaluate implementation using the RE-AIM framework as part of PRISM (Table 2), comparing Implementation as Usual to Active Implementation. We plan to start evaluation 6 months following the Consolidation phase at each site, to allow for 12 months for evaluation to provide longer-term information on Maintenance outcomes, a key gap in the literature [63, 64]. While our EBPs vary by specific clinical focus, location of intervention (e.g., clinic, home), personnel involved, and duration, they will all be part of a cohesive effort to shift care to be more consistent with an AFHS. Thus, we will examine each EBP in two ways. Across EBPs, we define our *primary implementation outcome* as Reach, since an AFHS is primarily defined by whether all older adults receive “Age-Friendly” care. Reach is defined as the proportion of Veterans eligible for each EBP that received that EBP during the implementation phase (Table 2). We will measure Reach aggregated to the cluster level across participating sites. We will also capture how frequently patients receive the first part of the intervention (i.e., screening or referral), but not the second part (i.e., full delivery of intervention). Our *primary effectiveness outcome* across EBPs is “facility-free days” or the number of days older Veterans remain alive and outside the hospital or nursing home (for post-acute or long-term care). We will evaluate this outcome among all Veterans eligible for at least one EBP as well as among EBP cohorts. Additionally, we will capture *secondary outco*mes specific to each EBP, using convergent mixed methods informed by the RE-AIM framework (Table 2). Maintenance will be measured across EBPs using our primary implementation outcome (Reach), analyzing whether the proportion of eligible Veterans enrolled in the EBPs is stable, improves, or declines by more than 10% at the time of Evaluation (1 year following Active Implementation).

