## Methods and design

### Overview of study design

To achieve our goals, we are conducting a randomized, type III hybrid effectiveness-implementation study using a stepped-wedge design to compare passive implementation or “implementation as usual” to facilitation as the primary implementation strategy [23, 24]. We selected facilitation as the primary implementation strategy because each EBP is multi-component and none have fully been used before in the VA, potentially necessitating a higher-intensity and flexible strategy [25, 26]. However, given the anticipated spread of the AFHS model in the VA, we decided to contrast this strategy with implementation “as usual,” which is less intensive and costly and more aligned with IHI’s model. The SAGE QUERI was designed for internal VA operational proposes. In January 2019, all planned procedures were determined by the VISN Chief Medical Officer to be operations activities not constituting research and proceeded as such under VISN authority and oversight without IRB review according to the provision of VHA Program Guide 1200.21.

Our primary effectiveness outcome is “facility-free days,” generally defined as days alive and outside a hospital or nursing home [27–29]. Our primary implementation outcome is Reach, defined as how many eligible Veterans receive each intervention. Unlike typical cluster trials that assign clusters of sites to a control/comparison condition or an active treatment condition, all sites in a stepped wedge design eventually receive the active treatment condition after receiving the comparison condition for a scheduled period [23, 24]. This design is ethically indicated in circumstances when equipoise is insufficient to justify the use of a control condition for the entire study period (e.g., when the principle of justice precludes withholding an intervention proven beneficial). Clusters are randomized to start time for the more active implementation phase. As shown in the Additional file 1: Figure S1, we plan to use three “steps” with each including three VA medical centers and their associated clinics, randomizing each cluster to a different start time for Active Implementation.

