### Target sites

All nine VA Medical Centers (VAMC) in VISN 4 and their associated outpatient clinics will be eligible to participate in the four EBPs to the degree appropriate for their site. For example, every site has pharmacists (which is critical to EMPOWER), and all nine VA Medical Centers have Home-Based Primary Care (HBPC) or home care agencies suitable for implementation of TAP and CAPABLE—but only five sites across VISN 4 perform intermediate or complex surgeries suitable for the Surgical Pause. For TAP, CAPABLE, and EMPOWER, we are randomizing at the VAMC-level, and for Surgical Pause, we are randomizing at the level of the surgical service line level to achieve balance between the 3 clusters regarding case volume, case complexity, and patient comorbidity. Each medical center can decide which EBPs to participate in, although we are encouraging medical centers to adopt all four, where applicable, adhering to the AFHS model.

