## Discussion

The overall goal of the SAGE QUERI program is to understand how best to implement and scale evidence-based practices aligned with the AFHS model within the VA. SAGE QUERI expands on prior Age-Friendly work by identifying four evidence-based interventions to address core tenets (4Ms) of the AFHS initiative, rigorously evaluating different implementation strategies, and assessing a clinically meaningful outcome across all four EBPs. The primary outcome—“facility free days”—is aligned with the goals of older adults to live independently in the community as they age, and with system and payer needs to reduce costs. We will test the effectiveness of implementation strategies of implementation as usual compared with external facilitation, training and technical assistance, intervention tailoring, and audit and feedback, while providing valuable information about the cost effectiveness of each intervention. Together, the SAGE QUERI program will provide an implementation model of AFHS-concordant care across an entire regional healthcare system, offering insights for replication across the VA in fulfillment of its operational commitment to becoming a nation-wide AHFS.

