A second set of potential challenges is that sites may not choose to implement all four EBPs, despite our hypothesis that implementing all four EBPs are likely to have synergistic effects across the 4Ms, and thus a greater impact on the primary clinical and implementation outcomes. To increase feasibility of adoption for each medical center, we have conceptualized and chosen EBPs that do not rely on a single site of practice (e.g., primary care or geriatrics departments) to be responsible for implementing all four interventions. Our goal is to have the EBPs employed in every clinical setting to which they apply (for example, Surgical Pause could be disseminated to inpatient surgery and to non-surgical procedural specialties) in the nature of the AFHS model. In addition, we strategically selected EBPs that align with VA national initiatives. Additionally, using preliminary data, we identified potential adaptations to the interventions that may overcome these barriers. For example, the TAP and CAPABLE models are led by occupational therapists (OTs). The VA employs OTs and also contracts with OTs employed by outside agencies to provide home-based care for Veterans. We thus have the option to implement these interventions using VA staff or by training contracted staff. These decisions have trade-offs but contribute to the rich contextual inquiry and are likely applicable trade-offs to other VA sites—such as generating knowledge to medical centers that differ in approaches for employing OTs.

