## Anticipated contributions to practice

To our knowledge, this is the first large-scale randomized effort to implement AFHS aligned evidence-based practices in a national health care system. Given the pressing need to improve care delivery for older adults, we anticipate findings from this project will be timely and relevant. Deliverables include not just knowledge about how each EBP might be most successfully disseminated and implemented in the VA, but how they might affect novel outcomes (e.g., days at home), how each varies in terms of costs and changes in outcomes, and best practices for expansion beyond VISN 4 (even within a pandemic). Although this work was designed to be implemented internally within the VA for operational purposes, we plan to partner with the IHI and the John A. Hartford Foundation, as well as our Veteran Advisory Board and Technical Expert Panel, to create and deliver VA-specific toolkits hosted by IHI and the John A. Hartford Foundation on the national Age-Friendly initiative website, as well as on the websites of our national VA partners (GEC and National Surgical Office). We will also deliver VA-specific toolkits to be hosted by the Canadian Deprescribing Network and by TAP and CAPABLE directors and institutions. Each toolkit will contain a collection of materials including written documents, videos, and links aimed at educating VA leadership and clinicians about the AFHS model and implementation of each of the four EBPs. We will also incorporate materials designed for use in our Implementation as Usual phase, to assist future users in spreading the AFHS approach. Moreover, we will create “patient-facing” guides as a resource for Veterans and caregivers; emerging evidence suggests these resources can act as a “pull” mechanism for Dissemination as they create demand in the targeted populations [75]. Ultimately, we plan on reaching out to other VISNs with the goal of spreading these EBP nationally.

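### TAP, CAPABLE and EMPOWER share one medical-centre randomisation and one phase term, so facility-free days and downstream costs in an EBP cohort cannot be credited to that EBP in co-eligible Veterans

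*Protocol article*

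**What the plan says.** **Randomisation.** Overview of study design describes three steps of three medical centres each, "randomizing each cluster to a different start time for Active Implementation". Target sites adds: "For TAP, CAPABLE, and EMPOWER, we are randomizing at the VAMC-level". Surgical Pause is handled separately: "for Surgical Pause, we are randomizing at the level of the surgical service line level". Each centre may choose its evidence-based practices (EBPs) but is encouraged to take all four.

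**Phases and model.** Under Study phases, "each site will move through five consecutive phases". Quantitative evaluation defines treatment as one binary variable, before versus after Active Implementation. It describes no term specific to an EBP.

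**Outcome populations.** Phase 5 makes facility-free days the primary effectiveness outcome and says: "We will evaluate this outcome among all Veterans eligible for at least one EBP as well as among EBP cohorts".

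**What is promised.** The Discussion speaks of "providing valuable information about the cost effectiveness of each intervention". Anticipated contributions to practice lists "how each varies in terms of costs and changes in outcomes" among the deliverables. The Discussion also hypothesises that "implementing all four EBPs are likely to have synergistic effects across the 4Ms".

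**Costs.** The economic evaluation section plans to report the cost of each intervention, with staff time taken from personnel data and project records, and also costs or savings from later health care use.

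**The concern.** If a medical centre enters Active Implementation for several EBPs together, a Veteran eligible for more than one meets all of them at the same crossover. The phase coefficient in the cohort named after one EBP then also carries whatever the others do in those Veterans. An EBP with little effect could borrow another's effect, or a useful one could be masked.

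This matters because the article means to say something about each EBP. Besides the two promises quoted above, the Background names uncertainty about which 4M interventions have the most impact as a gap, and presents the programme as a response to the gaps it lists. A reader of the results will be inclined to rank the EBPs by their cohort estimates.

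**Working it through.** The article gives no figure for eligibility overlap or for an EBP-specific effect, so there is no stated number to reproduce. The check covers whether the EBPs can be separated, whether overlap is possible, and how large the mixing could be.

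**1. Can the design separate the three EBPs?**

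Inputs: nine medical centres and four periods (Power analysis), and three steps of three centres (Overview of study design). Build the centre-by-period design matrix with 9 centre columns, 3 time columns and one on/off column for each of TAP, CAPABLE and EMPOWER, giving 9 + 3 + 3 = 15 columns.

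| Scenario | Rank | Meaning |
|---|---|---|
| Shared start, all three EBPs run at every centre | 13 of 15 | The three EBP columns are identical (9 + 3 + 1 = 13); only the joint effect is estimable |
| Shared start, assumed partial adoption (one EBP at all nine centres, the other two at six each) | 15 of 15 | Separable, but only through the centres' own choice of EBPs |
| Start randomised separately for each EBP (one illustrative draw) | 15 of 15 | Separable by randomisation |

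Under a shared start, adding EBP-specific terms to the model would therefore not recover a randomised contrast for each EBP.

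**2. Can eligibility overlap?**

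From Table 3 and Target population:
- TAP needs a dementia diagnosis, a willing caregiver and participation in at least two basic ADLs.
- CAPABLE needs low income, at least one ADL or two IADL deficits, and independent movement about the house.
- EMPOWER needs a targeted drug for 90 of the last 120 days.
- Exclusions are hospice, long-term nursing home residence, severe mental illness (EMPOWER) and no caregiver (TAP).

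None of these bars eligibility for two or three EBPs. TAP and CAPABLE also share home care as a possible setting.

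**3. How large is the mixing?**

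Let d_X be the effect on facility-free days of facilitating EBP X compared with usual implementation, averaged over all eligible Veterans whether or not they received it. Let d_O be the same for the other EBPs run at the centre, and p the co-eligible share of cohort X. Assuming additive effects and no spillover:

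cohort effect = d_X + p × d_O, so cohort effect / d_X = 1 + p × r, where r = d_O / d_X.

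| p (assumed) | r = 0.5 | r = 1 | r = 2 |
|---|---|---|---|
| 0% | 1.00 | 1.0 | 1.0 |
| 10% | 1.05 | 1.1 | 1.2 |
| 30% | 1.15 | 1.3 | 1.6 |
| 50% | 1.25 | 1.5 | 2.0 |
| 100% | 1.50 | 2.0 | 3.0 |

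For an inert EBP (d_X = 0) the apparent effect is p × d_O. With p assumed at 20–60% and d_O at 2–6 days, it runs from 0.2 × 2 = 0.4 to 0.6 × 6 = 3.6 days.

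The upper end is demanding. If facilitation raised Reach by 30 percentage points (assumption), d_O = 6 would need 6 / 0.3 = 20 days per recipient. A 6-day effect per recipient would instead give d_O = 0.3 × 6 = 1.8, and a borrowed effect of 0.2 × 1.8 = 0.36 to 0.6 × 1.8 = 1.08 days.

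If the EBPs are synergistic, as the article expects, the additive formula understates the mixing.

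**The case against.** The strongest reply is that this is a type III hybrid trial comparing implementation strategies. Phase 5 contrasts Implementation as Usual with Active Implementation, treats the EBPs as one effort, and makes facility-free days primary across them. The sentence on EBP cohorts only names populations; it does not say that a cohort's coefficient isolates an EBP. Read as the effect of facilitating whatever the site offers, among Veterans eligible for X, the analysis is valid. That stands, and it is why the remedy is mainly a label. It does not cover the two statements about each intervention.

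Three stronger readings are tempting but not supported:
- *All three EBPs start on the same day for every Veteran.* One start per cluster is the natural reading of the sections on design, sites and phases taken together, but no sentence gives one date for all three EBPs. The supplementary figure is not shown, centres may decline EBPs, and Active Implementation is a six-month period in which receipt varies.
- *The trial cannot show what each EBP costs.* Direct cost per intervention is to be reported. Only downstream costs or savings, and hence cost effectiveness, are affected.
- *The borrowed effect exceeds the detectable change of 1.7 days.* That figure is pooled across EBPs at 611 Veterans per centre. A single cohort is smaller and its detectable change larger, so it is the wrong benchmark.

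It is also fair to say that the overlap is unknown and might be small, that outcome changes in the closing section could include EBP-specific secondary outcomes, and that no passage makes national spread depend on cohort results. These points limit the size and the stakes.

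Handling of overlapping cohorts is often left to an analysis plan. Here, however, the randomisation unit, the treatment variable and the per-intervention promises are all stated in the article. No later analysis detail can make a shared start separate the EBPs by randomisation.

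**Conclusion.** The point holds in limited form. Where a medical centre runs more than one of TAP, CAPABLE and EMPOWER from a common start, the phase effect on facility-free days in an EBP cohort, and the matching downstream costs or savings, combine all EBPs facilitated there in co-eligible Veterans. For these three EBPs the randomisation does not support statements about the cost effectiveness of each one, or about how each changes facility-free days. Partial adoption does not rescue them, because it rests on self-selection.

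The size scales with an overlap that the article does not give: no distortion at zero overlap without spillover, and 1.1 to 1.5 times the own effect at 10–50% overlap if the other EBPs together match it. The conclusion assumes a shared start per cluster, and the multiples assume additive effects.

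Reach per EBP, direct intervention costs and the pooled comparison of strategies stand as planned. Surgical Pause, randomised by surgical service line, is outside this point.

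**What to change.** 1. Label each TAP, CAPABLE and EMPOWER cohort result as *effect of facilitating all EBPs offered at the site, among Veterans eligible for X*, for both facility-free days and downstream costs or savings. This is the essential step.
2. Report the eligibility overlap among the three cohorts, and which EBPs each centre ran.
3. Add a supportive term to each cohort model: phase × (eligible for another EBP randomised by medical centre, at cohort entry). Show the phase effect in Veterans eligible for X only. State that these Veterans are a narrower population, that intervals will be wider, that site-level spillover remains, and that the contrast is still facilitation against usual implementation. This stratum should not be the sole basis for a claim about an EBP.
4. Narrow the statements in the Discussion and in Anticipated contributions to practice to direct costs, Reach and outcomes under facilitation of the EBPs offered.

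The cost is wording, one overlap table and one interaction term per cohort model. The eligibility flags are already needed to define the population eligible for at least one EBP. Randomisation and data collection do not change.
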